### Anthropometric measures

Height and weight measurements will be taken to allow BMI to be calculated. A waist measurement will also be taken as an indicator of obesity [15]. Height will be measured without shoes to the nearest 0.1 cm using a stadiometer (Wedderburn Portable Height Rod, Model WS-HRP). The participant will be required to stand with their heels touching the vertical foot panel of the stadiometer and the participant’s head held in the Frankfort plane. Weight will be measured in bare feet or socks (without shoes) using a calibrated balance scale (Tanita Digital Scales, Model HD-351) with the participant dressed in light clothing, and any clothing pockets emptied. Waist circumference will be measured to the nearest 0.1 cm equidistance between the last palpable rib and the top of the superior border of the iliac crest with the tape perpendicular to long axis of body and parallel to ground at the end of expiration [16,17]. The patient will be requested to place their arms relaxed by their side for this measurement. A narrow 7 mm wide flexible steel anthropometrical tape measure (Rosscraft) will be used.

### Psychological distress or well-being

Psychological distress or well-being (including mood and anxiety disorders) will be screened for using the 6-item Kessler6 (K6). A unidimensional factor structure has been supported in a large Australian community population [18] and the validity of the K6 has been supported for screening serious mental illness [19] as well as for discriminating between people with and without psychological distress in the community [20].

### Disease burden and number and type of comorbid conditions

Disease burden and the number and type of comorbid conditions will be measured using a self-report comorbidity measure [21]. Using the comorbidity measure [21] 25 common chronic diseases (excluding depression) are rated for the degree to which each condition interferes with daily activities. Scores on this measure have been found to correlate more strongly with health state measured using the SF-36 than other comorbidity indices in community samples [22,23].

### Perceived functional and structural social support

Perceived functional and structural social support will be measured using the Medical Outcomes Study Social Support Survey [24]. This measure was designed for research with people with chronic conditions [9] and testing by the authors has supported validity for use among people with chronic diseases including support for four social support subscales [24].

### Physical function

Physical function will be measured using the Timed Up and Go Test (TUG) as an objective measure of functional mobility [25]. Psychometric testing has supported use of the TUG as a measure of functional mobility in older adults [26-28]. Responsiveness of the TUG has been supported in a study of geriatric patients attending day hospital [29] and sensitivity to change has been supported among people with chronic diseases [30,31].

### Self-reported health perception

Self-reported health perception will be measured using a single question where participants rate their health on a 1 to 5 point scale as excellent to poor respectively [32]. Strong support exists for the ability of a single question regarding self-reported health perception to reflect the current, changing and future health status of people with chronic disease [32].

### Sociodemographic and intervention data

Demographic data collected only at baseline will include: age, gender, indigenous status, country of birth, language (other than English), marital status, home ownership, highest level of education, occupation, and employment status. Home ownership, highest level of education and occupation will be used as socioeconomic indicators. Intervention data collected will include the length and type of intervention received (for example, back school program, gym program, diabetes education, or the professional seen).

### Sample size and power

A minimum sample size of 130 participants is required to examine the change over time from baseline to 12-months post-intake of the SF-36; using a one-group longitudinal design, a power of 80% with a two-sided type 1 error of 5% to detect a difference of at least 5 points in the social functioning scale of the SF-36 using a t-test [33]. Three to five points of change in SF-36 scores has been reported as the minimally clinically important difference [33,34] and is equivalent to a small effect size for those with chronic diseases [34]. A small effect size is anticipated for changes in health over 12-months based on the small to large effect sizes found in treatment effectiveness studies using the SF-36 in related chronic disease studies over similar times [7,12,34,35] and the high percentage of clients with multiple chronic diseases attending the service prior to the study commencement, for whom moderate to large effect sizes are unlikely. The sample size calculation was based on the social functioning scale of the SF-36 as this outcome would likely show the smallest difference and therefore need the largest sample size. Therefore, provided the study sample size exceeds 130 participants, this investigation should have greater than 80% power for all outcomes.

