#### ***Hypotheses***

1. Health will be maintained or improve over time from intake (baseline) to 12-months after intake with a small average effect size anticipated for improvement (effect size ≤ 0.2).

2. Health outcomes will be moderately to strongly and negatively associated with the number of chronic diseases (effect size ≥ 0.5).

3. Days in hospital and inpatient admission costs will decrease after intake to the service compared with before intake to the service.

4. The health of clients attending the service will be worse than the general population using Australian population normative data at all times (effect size ≥ 0.2).

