Adjustment will made for wave missing data (where a subject misses an entire visit) using inverse probability weighting [38]. This is a two-stage procedure. In the first stage a logistic regression model is used to predict which subjects are more likely to be missing at each follow-up time. This model will include time, demographic factors and comorbidity factors collected at baseline. The probability of each subject being missing at each time is then calculated and inverted to create a weight that can be used in the regression models described above. As an example, if men at 12-months have a 0.5 probability of responding, then the weight for men is 2 so that the results for those men who responded at 12-months are doubled. This will enable a sensitivity analysis with comparison to the complete case analysis to be conducted.

The health of the study sample (using SF-36 scores) will be compared to Australian normative data [39] matched on select sociodemographic variables such as age, gender and select chronic diseases using unpaired t-tests with 95% confidence intervals.

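### The claim of more than 80% power for all outcomes rests on one calculation, a 5-point change in SF-36 social functioning, and does not carry over to the others

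*Protocol article*

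**What the plan says.** All of this is in the Protocol article. Under Sample size and power, the starting point is: "A minimum sample size of 130 participants is required to examine the change over time from baseline to 12-months post-intake of the SF-36". The target is "to detect a difference of at least 5 points in the social functioning scale of the SF-36 using a t-test", in one group, with 80% power and a two-sided 5% type 1 error. No SD is given. The same section reports the size of change that matters: "Three to five points of change in SF-36 scores has been reported as the minimally clinically important difference", and calls that a small effect.

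The step from this one scale to everything else is the argument that "this outcome would likely show the smallest difference and therefore need the largest sample size". From it follows: "Therefore, provided the study sample size exceeds 130 participants, this investigation should have greater than 80% power for all outcomes".

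Three other sections bear on this:

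- **Hypotheses.** Hypothesis 1 expects health to be maintained or to improve, "with a small average effect size anticipated for improvement (effect size ≤ 0.2"). Hypothesis 4 sets an effect size of at least 0.2 for the deficit against Australian norms. Hypothesis 3 predicts fewer hospital days and lower inpatient costs.
- **Data analysis.** The comparison with norms uses unpaired t-tests. Cost, hospital days and admissions are modelled as Poisson. Missed visits are provided for: "Adjustment will made for wave missing data (where a subject misses an entire visit").
- **Participants and selection criteria.** Follow-up data enter the effectiveness analyses only for clients who attended at least one intervention session.

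**The concern.** A power statement for all outcomes needs either a calculation for each outcome or a valid argument that the one calculated is the worst case. The article gives a single calculation. Its worst-case argument looks only at the size of the difference, whereas the required number depends on the difference divided by its SD. The article's own hypotheses and its own important range also include effects smaller than the one that 130 can detect with 80% power.

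The study is meant to inform services and to be a platform for later trials. A reader who takes the sentence at face value would treat a non-significant result on any outcome as coming from an adequately powered study. For several of the effects that the article names, that is not established.

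**Working it through.** **Inputs from the article:** n = 130; two-sided 5%; 80% power; one-group t-test; target 5 points; important range 3 to 5 points; effect size at most 0.2 (Hypothesis 1) and at least 0.2 (Hypothesis 4). **Not in the article:** the SD of change, the unit of the 0.2 in Hypothesis 1, the baseline-to-12-month correlation, and any loss rate. These are back-solved or assumed below, and marked so.

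**1. What 130 delivers.** For a paired test, n = ((1.960 + 0.842) × SD / difference)². Solving for the standardised change gives d = 2.802 / √130 = 0.246. The exact non-central t gives d = 0.248. With 5 points, the implied SD of change is 5 / 0.2476 = 20.2. So 130 is consistent with the stated design if the SD of change is about 20. Since no SD is stated, the figure cannot be checked further.

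**2. The article's own important range** (non-central t, n = 130, implied SD 20.2):

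| Change | d | Power | Pairs for 80% |
|---|---|---|---|
| 5 points | 0.248 | 80% | about 130 |
| 4 points | 0.198 | 61% | 203 |
| 3 points | 0.149 | 39% | 358 |

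**3. Hypothesis 4, unpaired, at its threshold of 0.2.** If the normative mean were known without error, power is Φ(0.2 × √130 − 1.960) = Φ(2.280 − 1.960) = Φ(0.320) = 0.63. This is a ceiling. With a normative sample of only 130 it is 36%. Reaching 80% at 0.2 needs about 197 clients even with a very large normative sample. Within-person correlation plays no part in this test.

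**4. Hypothesis 1 at 0.2.** The answer depends on the unit.

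- In SD-of-change units, power at n = 130 is 62%, and 199 pairs are needed for 80%.
- In baseline-SD units, d = 0.2 / √(2(1 − r)), where r is the baseline-to-12-month correlation (assumed). Power is 48% at r = 0.3, 62% at 0.5, 72% at 0.6 and 83% at 0.7. The break-even is r = 1 − (0.2 / 0.2476)² / 2 = 0.67.

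**5. The worst-case argument.** Hold the difference at 5 points and vary the SD of change (assumed values, for illustration). At SD 25, d = 0.20 and power is 62%. At SD 30, d = 0.167 and power is 47%. A scale with the same or a somewhat larger difference can therefore need more participants than social functioning if it is more variable.

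**6. Hospital days, admissions and costs.** No rate, dispersion or target effect is given, so no power can be computed. A t-test on an SF-36 scale says nothing about it.

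**7. Enrolled or analysed.** If 130 were the number enrolled, a paired test for 5 points would have these powers (assumed losses):

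| Loss | Pairs | Power | Enrolment to keep 130 pairs |
|---|---|---|---|
| 10% | 117 | 76% | 145 |
| 20% | 104 | 71% | 163 |
| 30% | 91 | 65% | 186 |

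**The case against.** The defence has several fair points.

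- **Powering at 5 points is a legitimate, openly stated choice.** This stands. The 39% at 3 points is no error in the 5-point calculation; it only shows that the result does not generalise.
- **Hypothesis 1 need not conflict with 130.** A reader might infer that an anticipated effect of at most 0.2 flatly contradicts a design needing 0.248. The article does not support that, because it gives no standardiser. If 5 points corresponds to 0.2, the baseline SD is 25, and a correlation of about 0.67 or more restores 80%. The article states neither unit nor correlation, so it establishes neither the conflict nor the claim.
- **Hypothesis 4's 0.2 is a floor.** With an error-free norm, a true gap of 0.25 gives Φ(0.25 × √130 − 1.960) = Φ(0.890) = 81%. With 97% multimorbidity reported in the service's first year, a larger gap is plausible. This stands too, but the claim of power for all outcomes carries no such condition and fails at the threshold that the article names.
- **A reader might infer that 130 is the number enrolled and that recruitment could stop there.** The article never says so. It calls 130 a minimum needed to examine change to 12 months, which may well mean participants contributing that change. Only the ambiguity can be criticised. The loss figures are also for complete pairs, whereas the planned mixed models use the 3- and 6-month scores of clients who miss 12 months.
- **The SDs of 25 and 30 are assumptions.** They show that the worst-case argument is invalid, not that any particular scale is underpowered.

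**Conclusion.** The statement that any sample above 130 gives more than 80% power for all outcomes is unsupported and should not stand as written. Firmest are the ceiling of about 63% at Hypothesis 4's threshold, which needs no assumed SD or correlation; the absence of any calculation for the hospital and cost outcomes; and the invalid inference from smallest difference to largest sample. The 39% at 3 points and 61% at 4 points rest on the SD of 20.2 implied by 130. The 62% for Hypothesis 1 holds only in SD-of-change units. The 71% after 20% loss holds only if 130 means enrolled, and the loss rate is an assumption.

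It does not follow that the 5-point calculation is wrong, or that most outcomes are shown to have low power. For many of them the article gives too little to say. The study offers preliminary evidence and the remedy changes no analysis, so this should be fixed but is not critical.

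**What to change.** In Sample size and power:

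1. Delete the claim of more than 80% power for all outcomes and the smallest-difference rationale.
2. State the SD of change that the authors used. The 20 or so found here is back-solved and should serve only as a check on it.
3. Say that 130 is the number of participants with both baseline and 12-month SF-36 data, and that it gives 80% power for a 5-point change at that SD. If it was meant as the number enrolled, say so and give the expected loss.
4. Add the power for 4 and 3 points (about 61% and 39% at an SD of about 20) and for 0.2 against norms (at most about 63%). State the unit of the 0.2 in Hypothesis 1.
5. Describe the hospital, cost and other outcomes as estimated with confidence intervals and not powered.

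This is a wording change. It needs no extra participants and alters no analysis. Its one cost is that the stated power becomes less favourable.

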### Data analysis

Descriptive statistics and exploratory plots (boxplots or histograms) will be used to describe the outcome variables (e.g., health state, preference based measure of health, hospital utilisation, and costs) and potential predictors (e.g., age, employment status).

SF-36 scale raw scores will be transformed to a 0 to 100 scale. Results will be analysed using the 8 scales and the summary scores where appropriate. Scatterplots of the relationship between variables will be examined to check for linearity or potentially non-linear associations. Mean SF-36 scores will be plotted over time by demographic and disease subgroups to visually examine chronic disease progression. Regression models will be used to examine the effect of time and predictors on post-intake SF-36 scores. The scores will be modelled at 3- to 12-months with the baseline score as a predictor in order to: i) analyse the change from baseline; ii) help control for regression to the mean [36]. Mixed models will be used with subject-specific intercepts to model the dependence in results over time from the same subject. The lasso technique will be used to choose the best set of predictor variables from an initially large set of potentially important variables [37]. The residual distribution of the best model will be examined to check that it is approximately normally distributed with no large outliers. The count outcome variables (i.e., cost, days in hospital, and number of hospitalisations) will be analysed using the model described above but assuming a Poisson distribution.

The predictors to be examined in all of the models will be: BMI and waist measurement, disease burden, number and type of comorbidities, self-reported health perception, age, gender, indigenous status, country of birth, language (other than English), marital status, home ownership, highest level of education, occupation and employment status, length and type of intervention; and baseline psychological distress or wellbeing, functional and structural social support, and physical function. Health (measured using the SF-36) and the preference based measure of health will be examined as predictors for count outcomes.

Adjustment will made for wave missing data (where a subject misses an entire visit) using inverse probability weighting [38]. This is a two-stage procedure. In the first stage a logistic regression model is used to predict which subjects are more likely to be missing at each follow-up time. This model will include time, demographic factors and comorbidity factors collected at baseline. The probability of each subject being missing at each time is then calculated and inverted to create a weight that can be used in the regression models described above. As an example, if men at 12-months have a 0.5 probability of responding, then the weight for men is 2 so that the results for those men who responded at 12-months are doubled. This will enable a sensitivity analysis with comparison to the complete case analysis to be conducted.

The health of the study sample (using SF-36 scores) will be compared to Australian normative data [39] matched on select sociodemographic variables such as age, gender and select chronic diseases using unpaired t-tests with 95% confidence intervals.

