## Discussion

This study is a broad evaluation of the client health outcomes and healthcare costs of people attending a unique regional service that is attempting to meet the health needs of regional and rural Australians with chronic disease. The study will provide preliminary evidence on the effectiveness of interdisciplinary intervention for this clinical population; an area that has received little investigation to date [8]. In addition, it will provide evidence regarding the influence of a range of variables including multimorbidity on the health and health costs of people with chronic disease in a rural and regional area. Comparison of the health state of people attending the service to the general population will determine the severity of health issues in the study population. The combined evidence will greatly assist in informing future service delivery and research.

The need for rigorous non-randomised studies in community settings has been highlighted by Bettger and Stineman [40] as these studies can identify target populations and appropriate outcomes for measurement that are important foundations for randomised controlled trials (or can even inform if randomised trials are required at all). Of relevance to the many participants with multimorbidity who are likely to be recruited in this study, randomised controlled trials to evaluate long-term outcomes have been discussed as inappropriate for people with conditions likely to worsen over time regardless of the intervention received [40]. Thus this longitudinal study will provide important information on the progressive impact of chronic disease in people in regional and rural areas who are involved in this unique intervention program. Specifically, the study will contribute knowledge about hospital use, health and healthcare costs associated with chronic disease for people in regional and rural areas over time. The factors that influence these changes will also be investigated.

Economic and health-related outcomes from this investigation will inform other health services throughout Australia (and elsewhere) who are considering adopting comparable models of service delivery. Outcomes from this study will also inform future research investigating health service needs and clinical needs for comparable populations.

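### The SF-36 predictor model holds baseline SF-36 fixed, so its disease-count coefficient does not estimate the Hypothesis 2 association and cannot be judged against 0.5

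*Protocol article*

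**What the plan says.** Under Hypotheses, the second item reads "Health outcomes will be moderately to strongly and negatively associated with the number of chronic diseases", with an effect size of at least 0.5. The metric of that effect size (correlation, standardised slope or standardised mean difference) is not stated. Aim 2 asks how comorbidities and other factors affect health state up to 12 months after intake.

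Under Data analysis, the SF-36 model is specified as follows: "The scores will be modelled at 3- to 12-months with the baseline score as a predictor". The stated reasons are to "i) analyse the change from baseline; ii) help control for regression to the mean". Repeated visits are handled thus: "Mixed models will be used with subject-specific intercepts to model the dependence in results over time from the same subject". The candidate predictors begin "BMI and waist measurement, disease burden, number and type of comorbidities, self-reported health perception, age, gender", and selection is by lasso: "The lasso technique will be used to choose the best set of predictor variables from an initially large set of potentially important variables". Scatterplots and plots of mean scores by disease subgroup are also planned, but these are descriptive. SF-36 scores are compared with population norms by unpaired t-tests, and Hypothesis 4 applies that comparison at all times. No predictor model has baseline SF-36 as an outcome.

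The Discussion promises of changes over time: "The factors that influence these changes will also be investigated".

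**The concern.** Clients with more diseases are expected to arrive with lower SF-36 scores. Much of the association that Hypothesis 2 describes is therefore already in the baseline score. Entering that score as a covariate removes this part and leaves a remainder. A reader who sets the remainder against 0.5 is comparing two different quantities.

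The coefficient is also open to a second misreading. Because the adjustment is described as a way to analyse change, a negative coefficient is likely to be reported as disease count influencing change. Yet such a coefficient arises even when clients with many and with few diseases change by the same amount on average.

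The Abstract says the study will determine which factors future observational studies must control for, and the Discussion presents the influence of multimorbidity as a main product. Both depend on what this coefficient means.

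**Working it through.** **The plan's own figure.** Sample size and power gives 130 participants, a 5-point difference, 80% power, two-sided 5% and a one-group t-test, but no SD. The figure can therefore only be inverted:

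- Normal approximation: d = (1.960 + 0.842)/√130 = 0.246, so the SD of change is 5/0.246 ≈ 20.3.
- Noncentral t: d = 0.2476, so the SD of change is 5/0.2476 ≈ 20.2.

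**What this implies for rho**, the correlation between baseline and follow-up scores. With equal variances, SD(change)² = 2·SD²·(1 − rho), so rho = 1 − 20.2²/(2·SD²). The same section equates 3 to 5 points with a small effect size. Taking small as 0.2 is an assumption, prompted by Hypothesis 1:

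| Points equal to 0.2 SD | SD | Implied rho |
|---|---|---|
| 3 | 15 | 0.09 |
| 4 | 20 | 0.49 |
| 5 | 25 | 0.67 |

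The document therefore does not fix rho.

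**Effect of the baseline covariate.** Let disease count be fixed over time and correlate r with SF-36 at every visit. The standardised coefficient given the baseline score is

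beta = (r − r·rho)/(1 − r²) = r × (1 − rho)/(1 − r²).

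For r = −0.5 the multiplier is (1 − rho)/0.75. The last two columns come from 3,000 simulated studies per row, with n = 130 and three equally correlated follow-ups:

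| rho | beta | Share kept | Estimate at or beyond −0.5 | Differs from zero at 5% |
|---|---|---|---|---|
| 0.3 | −0.47 | 93% | 27% | about 100% |
| 0.5 | −0.33 | 67% | 0.3% | over 99% |
| 0.6 | −0.27 | 53% | 0% | 99% |
| 0.67 | −0.22 | 44% | 0% | 97% |
| 0.8 | −0.13 | 27% | 0% | 80% |

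The loss exceeds half when (1 − rho)/0.75 < 0.5, that is, rho > 0.625. There is no loss when rho ≤ 0.25. At the implied rho of 0.09, beta would be −0.5 × 0.91/0.75 = −0.61. Without the baseline covariate the simulated coefficient averages −0.50 and lies at or beyond −0.5 in about half of studies.

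**If 0.5 means a standardised mean difference**, r = 0.5/√(0.25 + 4) ≈ 0.243 in size. The loss exceeds half when rho > 1 − 0.5 × (1 − 0.243²) ≈ 0.53. The coefficient then differs from zero in 61% of simulated studies at rho 0.5 and in 36% at rho 0.67.

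**Reading as change.** In these scenarios the covariance of disease count with (follow-up − baseline) is proportional to r − r = 0, so disease count is unrelated to the change score. The baseline-adjusted coefficient is still −0.22 at r = −0.5 and rho 0.67, and it is significant in 97% of simulated studies.

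**The case against.** A reader might infer that Hypothesis 2 would be rejected even when true at its threshold. The documents do not support that. They give no rule for accepting or rejecting it. Under a rule that compares the point estimate with 0.5, even the unadjusted estimate fails about half the time when the truth is exactly 0.5. On the correlation reading, the planned model would usually find a negative coefficient that differs from zero.

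A reader might also infer that the association always shrinks by more than half. That needs rho > 0.625. Only the 5-point end of the plan's 3-to-5-point range gives such a value.

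Three further arguments have weight:

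- Baseline adjustment is deliberate and justified in the text, and Aim 2 concerns health after intake. The choice between a baseline-adjusted and a change-score analysis in non-randomised groups is a recognised choice of estimand. The significant coefficient above is thus a real conditional association and not a false positive. This stands, but it does not put that coefficient on the scale of the Hypothesis 2 threshold.
- Table 1 schedules the comorbidity measure at all four visits, so the model may use a time-varying count. The multiplier would then not apply as given. Conditioning on baseline health would still change the quantity estimated.
- The article condenses a fuller plan, which might contain an unadjusted correlation. However, the article itself fixes the outcome, the baseline covariate, its purpose and the predictor list, and the model so fixed does not answer the stated hypothesis.

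**Conclusion.** The mismatch holds. For SF-36, the only inferential predictor model estimates the association that remains after baseline health is fixed, whereas Hypothesis 2 concerns the strength of the association itself. The coefficient cannot be judged against 0.5, nor does it by itself show an effect on the change score.

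The size depends on assumptions. With r = −0.5 at every visit and a fixed disease count, the coefficient is about −0.33 at rho 0.5, −0.27 at 0.6, −0.22 at 0.67 and −0.13 at 0.8. The protocol gives neither rho nor the metric of the 0.5. Competition from disease burden and self-reported health perception, together with lasso shrinkage, would probably reduce it further; this was not computed.

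The point concerns the size and meaning of the coefficient. Baseline SF-36 does feature in the comparison with norms, so the gap is confined to the predictor models.

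**What to change.** Keep the baseline-adjusted model for its stated purpose. Add one prespecified model for Hypothesis 2:

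- SF-36 at all four visits, baseline included, as the outcome, with the subject-specific intercept already planned.
- Number of chronic diseases at intake forced into the model, not left to the lasso.
- No baseline SF-36 covariate.
- The standardised slope or correlation reported with its 95% confidence interval, and the metric of the 0.5 threshold stated.
- A disease-count by visit term for the separate question of whether change differs with disease count.

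The choice of demographic adjustment can be left to the study team. The cost is a paragraph of analysis text and one extra model on data already collected.

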### Study design

A longitudinal cohort study focusing on the health outcomes and costs of patients with chronic diseases attending the service will be implemented. Patients will be evaluated at baseline (intake to the service), and at 3-, 6-, and 12-months after intake to the service. The 3- and 6-month follow-ups were included to evaluate short-term outcomes after commencement of the intervention. The 12-month follow-up was included to evaluate intermediate outcomes to pick up a potential delay in the positive impact of intervention on some dimensions of health. This study has been prospectively registered with the Australian and New Zealand Clinical Trials Registry (ACTRN12611000724976).

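### Subject intercepts alone impose equal correlation on unequally spaced SF-36 visits; if correlation decays with the gap, model-based standard errors are too small at 12 months and too large at 3 months

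*Protocol article*

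**What the plan says.** Under Study design, the protocol article sets the schedule: "Patients will be evaluated at baseline (intake to the service), and at 3-, 6-, and 12-months after intake to the service". It gives the last visit a purpose of its own: "The 12-month follow-up was included to evaluate intermediate outcomes to pick up a potential delay in the positive impact of intervention".

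Under Data analysis, the response is the set of post-intake scores: "The scores will be modelled at 3- to 12-months with the baseline score as a predictor". Time is a model effect: "Regression models will be used to examine the effect of time and predictors on post-intake SF-36 scores". Within-subject dependence is handled in one sentence: "Mixed models will be used with subject-specific intercepts to model the dependence in results over time from the same subject". No serial term, random slope, unstructured covariance or robust variance is named. The one model check named looks at the shape of the residual distribution and at outliers.

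Hypothesis 1 concerns the whole year: "Health will be maintained or improve over time from intake (baseline) to 12-months after intake". Sample size and power has the same target: "A minimum sample size of 130 participants is required to examine the change over time from baseline to 12-months post-intake of the SF-36". The article gives no standard deviation, within-subject correlation or variance by visit. It does not say whether time is categorical or linear, or which variance estimator is used.

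**The concern.** The article states a covariance structure, so this is a choice it has made and not a detail left for later. A random intercept with independent residuals implies one variance at all three visits and one correlation for all three pairs. Scores 3 months apart would ordinarily be expected to correlate more strongly than scores 9 months apart. The article also expects clients with multimorbidity whose conditions tend to progress, which is a reason to expect divergence over time.

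If that happens, the model averages over visits that differ. With baseline as a covariate, a decaying correlation means that baseline explains less at 12 months than at 3 months, so residual variance rises with time while the model pools it. At stake is the precision claimed for the 12-month result, which is the focus of hypothesis 1 and of the sample size. A check of residual normality would not reveal the fault.

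**Working it through.** **The plan's own figure.** The sample size section gives 130 for 5 points, 80% power and two-sided 5%, with no standard deviation. From n = ((1.960 + 0.842) × SD / 5)², the implied SD of change is 5 × √130 / 2.802 = 20.3 points. The normal formula returns 130 at that SD and the exact t version 132. The figure is attainable but cannot be verified, and nothing below depends on it.

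**Inputs.** From the article: visits at 0, 3, 6 and 12 months; baseline as covariate; an intercept-only structure; two-sided 5%. Assumed: all correlations, model-based standard errors, and visit as a category.

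**Formulas.** Let v_j be the variance at visit j and c_ij the covariance of visits i and j, after conditioning on baseline where stated.
- Change between two visits: the intercept-only model uses 2(mean v − mean c)/n for every pair. The true value is (v_i + v_j − 2c_ij)/n.
- Baseline-adjusted mean at visit j: the model uses mean v / n. The true value is v_j / n, where v_j = 1 − ρ_j² at unit variance and ρ_j is the correlation with baseline.
- Ratio k = model SE / true SE. Type I error = 2(1 − Φ(1.96k)).

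**Simple check, no conditioning.** Correlations (3–6, 6–12, 3–12) = (.65, .60, .55), mean .60. For 3 to 12 months, k = √(.40/.45) = 0.943 and type I error is 6.5%. For 3 to 6 months, k = √(.40/.35) = 1.069 and 3.6%. With (.70, .60, .50), the results are √(.40/.50) = 0.894 and 8.0%, and √(.40/.30) = 1.155 and 2.4%.

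**Stable subject effect, partial decay and noise.** A share s of the variance is a stable subject effect. Of the rest, 60% is serially correlated (r per 3 months) and 40% is noise. Worked case s = 0.3, r = 0.5:
- Correlations with baseline: 0.3 + 0.42 × (0.5, 0.25, 0.0625) = 0.510, 0.405, 0.326.
- Residual variances: 0.740, 0.836, 0.894; mean 0.823.
- 12-month mean: k = √(0.823/0.894) = 0.96, type I error 6.0%. 3-month mean: k = √(0.823/0.740) = 1.05.

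**Pure exponential decay.** Worked case r = 0.8 per 3 months:
- Correlations with baseline: 0.8, 0.64, 0.41.
- Residual variances: 0.360, 0.590, 0.832; mean 0.594.
- 12-month mean: k = √(0.594/0.832) = 0.845, type I error 9.8%.

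**Ratios k over the assumptions tried, conditional on baseline**

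| Assumption | 3-month mean | 12-month mean | 3–6 change | 3–12 change |
|---|---|---|---|---|
| Equal correlation and variance | 1.00 | 1.00 | 1.00 | 1.00 |
| Random slope, SD 0.02 to 0.04 SD units per month | 1.02 to 1.06 | 0.98 to 0.92 | 1.01 to 1.03 | 0.99 to 0.97 |
| Stable effect (s 0.3 to 0.7), partial decay (r 0.5 or 0.8), noise | 1.05 to 1.09 | 0.96 to 0.92 | 1.08 to 1.09 | 0.95 to 0.94 |
| Pure decay, r 0.5 to 0.9 | 1.09 to 1.39 | 0.95 to 0.80 | 1.19 to 1.34 | 0.92 to 0.84 |
| Common covariance 0.6; variances 1.3, 1.0, 0.8 at 3, 6, 12 months | 0.85 | 1.24 | 0.89 | 0.98 |

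In the third row, type I error is 6.0% to 7.1% for the 12-month mean and 6.3% to 6.5% for the 3- to 12-month change. Under pure decay with r = 0.9 it is 11.5% and 9.8%.

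**Simulation.** Random-intercept fits with categorical visit and a baseline covariate (n = 130, 300 runs, pure decay) agree in direction. With r = 0.8, k is 1.34 (3–6) and 0.85 (3–12), and rejection is 0.3% and 11%. With r = 0.7, k is 1.23 and 0.91, and rejection is 1.3% and 8.3%. With 300 runs, the rejection rates are approximate.

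**The case against.** The strongest reply is that the error is conditional. The article gives no correlations or variances by visit, and under equal correlation and variance there is no error. This stands. A reader might infer that the standard errors are wrong as a matter of fact, but the document does not support that. The last row of the table shows that even the direction is not fixed: if variance falls over time, the 12-month mean and the 3- to 6-month change both go the other way.

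Second, the article names no 3- to 6-month or 3- to 12-month contrast as a key estimate. This also stands. A reader might take the remark about delayed impact as a planned test of 12 against 3 months, but Study design specifies no such test. It does not dispose of the point, because pooling the residual variance also affects the baseline-adjusted 12-month mean, which is what hypothesis 1 addresses.

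Third, the variance estimator and the coding of time are unstated and may be settled elsewhere. If subject-clustered robust standard errors are already intended, the standard-error problem largely goes away. The intercept-only structure, however, is stated.

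Fourth, the largest figures need pure decay with no stable subject component, an extreme case. With a stable component the departure is modest. The study also describes itself as preliminary, and a random intercept is a common choice for three visits. These points limit the weight of the concern without removing it.

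**Conclusion.** The point holds in conditional form. The article commits the SF-36 models to one variance and one correlation across visits 3, 6 and 9 months apart, and names no check that would expose a different pattern. If correlation decays with the gap, variances are roughly equal before conditioning on baseline, and standard errors are model-based, precision is overstated for the 12-month mean and the 3- to 12-month change, and understated for the 3-month mean and the 3- to 6-month change.

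The likely size is modest: 4% to 8% on the 12-month standard error, so a nominal 5% test runs at about 6% to 7%. The upper end, under pure decay, is about 16% for the 3- to 12-month change and 20% for the 12-month mean. The lower end is zero. All sizes rest on assumed correlations. It is worth changing because the assumption is unsupported and unchecked, bears on the main 12-month question, and is cheap to drop.

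**What to change.** In Data analysis, for the final SF-36 models after lasso selection, replace the intercept-only structure as follows:
- Treat visit as a category and use an unstructured covariance over the three post-intake visits (3 variances + 3 covariances = 6 parameters).
- If that model does not converge, use a random intercept and slope, or a continuous-time autoregressive structure.
- Where inverse probability weights are used, report robust standard errors clustered by subject.

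The lasso step can stay as planned, since the change concerns only the model from which estimates and intervals are reported. Small-sample degrees of freedom and a baseline-by-visit term are optional additions.

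The cost is a sentence or two of text, four more variance parameters than the two of the intercept-only model (6 − 2), which the planned minimum of 130 participants can support, and slightly less precision if the correlations are in fact equal.
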